### Data analysis plan

#### Primary non-inferiority analyses

We hypothesize that disclosure of actionable results by digital-ROR, with access to a GC, can provide non-inferior short-term and longitudinal cognitive, affective, and behavioral outcomes, and lower costs. Primary effectiveness outcomes include: post-disclosure knowledge and cancer or cardio disease-specific distress. We will test whether the receipt of results differ between arms as a secondary analysis. Receipt of results is considered a health behavior. For the 2 primary analyses, we will apply non-inferiority tests to examine if access to digital-ROR is non-inferior to GC disclosure. We will conclude non-inferiority if the upper bound of the randomization effect 97.5% one-sided confidence interval [CI] for cross-sectional T1 responses do not cross a -0.45 standardized difference threshold (i.e., margin) for knowledge and a 0.2 standardized threshold (i.e., margin) for disease-specific distress in the direction that would suggest that digital-ROR is worse. A standardized difference is the difference after variables are scaled to have standard deviation (SD) one with respect to baseline SD. We based the margins on what might be considered clinically relevant effects given our pilot data. We will use intention-to-treat approaches, comparing randomized arms, with confirmation by per-protocol analyses (i.e. restricting sample to those who properly used the method of disclosure as assigned). We will only declare non-inferiority if both intention-to-treat and per-protocol analyses are consistent, as recommended [133, 134]. For the secondary outcome receipt of results, we will examine non-inferiority of proportions. We will declare non-inferiority if the upper bound of the randomization effect 95% one-sided confidence interval for receipt of results is < 10% in the direction that favors usual care. Since all participants will have the option to speak with a GC, we will conduct secondary as-treated analyses (i.e. based on whether genetic counseling was actually received in both arms).

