In secondary analyses, we will use T-tests and Fisher’s exact tests for superiority testing. We will assess balance of potential confounders (e.g. age, race, study site) between arms using T-tests or Fisher’s exact tests. We will use multiple linear regressions (continuous outcomes) and logistic regressions (presence of a behavior such as receipt of results or uptake of confirmation testing) to examine effects after adjusting for potential confounders inadequately balanced. For longitudinal analyses that include all three time points (T0, T1, and T2), we will estimate regressions by Generalized Estimating Equations (GEEs); we will include main and interaction terms between arm and time [135]. 

Intervention costs will be estimated for each study arm, and mean costs per participant will be reported. We will perform a benefit-cost analysis comparing the two study arms, where net benefit (or cost) of the intervention is estimated as the difference in mean downstream costs (i.e., savings in health care expenditures attributable to the intervention) minus the difference in mean intervention costs. In sensitivity analysis, we will vary both intervention cost items and the costs of downstream health care services over reasonable ranges and examine the impact on results. The time horizon of the benefit-cost analysis will be limited to the 12-month follow-period. We will not project longer-term outcomes, nor will we estimate the potential economic impact on family members of genetic test results in study participants, as these are beyond the scope of this study.

#### Sample size justification for aim 1

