We chose *n* = 255/arm so we could conclude non-inferiority of digital-ROR if randomization effects comparing the digital arm to GC arms at T1 do not show clinically relevant worsening in the web arm. We chose a margin of -0.45 standard deviation units for knowledge and 0.20 for distress since they are considered modest changes in behavioral research, and they are consistent with our pilot data. In preliminary data from our pilot study, the baseline knowledge standard deviation was 2.86 points. A -0.45 standard deviation difference * (times) 2.86 = -1.29 points. A 1.29 point worsening in the knowledge scale would not be considered a meaningful difference. For disease specific distress, the baseline standard deviation was 9.31 points. A 0.20 standard deviation difference * (times) 9.31 = 1.86 points. Again, a 1.85 unit worsening in the distress scale would not indicate a clinically relevant change.

Table 4 demonstrates potential allowable non-inferiority differences. We chose 2.5% Type I error by applying a Bonferroni correction to a 5% Type I error rate with 2 comparisons (5%/2 = 2.5%). We calculated power using simulations in R with confirmation using PASS 11 software. For our secondary outcome of receipt of results, we will declare digital-ROR effect non-inferior if the upper bound of the 95% one-sided confidence interval effect is less than 11% in a direction that would favor usual care. This has an approximate 5% non-inferiority Type I error rate and > 80% power over a range of plausible differences given our preliminary data (e.g. >55% promising rate seen in preliminary data versus < 44% discouraging rate, *n* = 255/arm). We assumed a binomial pooled standard error estimator. We do not correct for multiple testing of secondary outcomes.

**Table 4 Tab4:** Estimated non-inferiority power, 2.5% Type I error (1-sided), number = 255/group (510 total)

Variable	Biobank Wave 2 Pilot Study	Non-inferiority difference allowed	Non-Inferiority Type 1 Error Rate and Power
Knowledge	T1 Mean 13.20, SD = 2.59 GC arm T1 Mean 12.50, SD = 2.12 Web arm Web minus GC effect = -0.7 Baseline standard deviation = 2.86	-0.45 SD units * 2.86 base SD = -1.29 point margin	2.5% Type I error rate > 80% power with − 0.7 pilot data effect > 99% power with 0 point effect

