Disease-specific Distress	T1 Mean 6.22, SD = 5.72 GC arm T1 Mean 6.00, SD = 6.42 Web arm Web minus GC effect: -0.22 Baseline SD = 9.31	0.20 SD units * 9.31 base SD = 1.9 point margin	2.5% Type I error rate > 95% power with − 0.22 pilot data effect > 90% power with 0 point effect.

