#### Aim 3 analyses

We hypothesize that moderators will identify those who benefit more and less from the eHealth interventions and can inform policies for return of results. For moderation (i.e., effect modifiers), we will include in regressions described in Aim 1 an indicator variable for randomization arm, panel time indicators (for longitudinal models examining all three time points), the potential moderator variable, and all two-way and relevant three-way interactions among the arm/time/moderator variables [135]. To maintain power, we will examine non-time moderators separately.

Qualitative data will be analyzed using an iterative, deductive content analysis approach and CFIR as the coding framework [107, 110, 137]. The qualitative data will include: (a) participant surveys and key informant interviews; (b) notes and debriefing from our research team meetings. Guided by consensual qualitative methods [138, 139], two independent coders will review notes and assign responses to CFIR constructs. Using a convergent mixed-methods approach [140], we will merge quantitative and qualitative data, organized by the 5 CFIR domains to evaluate which constructs were associated with, or more prevalent among: (a) patients who used the digital interventions exclusively versus those who used digital interventions and requested a GC versus those who requested to speak with a GC and declined use of digital interventions, (b) participants who used chatbot options versus web-based options, (c) participants who had confirmation testing and clinical medical follow-up versus those who did not, and (d) those who shared results with multiple relatives versus those who did not, providing an opportunity to comprehensively evaluate facilitators and barriers to implementation of digital alternatives for return of actionable genetic research results in large biobanks and research cohorts. We will use descriptive statistics, correlations, and generalized linear models, assuming appropriate link and family functions, to examine quantitative variables associated with barriers and uptake. We will estimate longitudinal models by Generalized Estimating Equations.

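### The secondary longitudinal GEE treats T0 as a response with a free arm effect, so its arm-by-time terms are change-from-baseline contrasts that give away precision

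*Protocol article*

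**What the plan says.** The secondary analyses follow the primary tests in the Data analysis plan of the protocol article. On the repeated measures the article says "For longitudinal analyses that include all three time points (T0, T1, and T2), we will estimate regressions by Generalized Estimating Equations (GEEs" and then that "we will include main and interaction terms between arm and time". The Aim 3 analyses section reuses the Aim 1 regressions and describes their time terms as "panel time indicators (for longitudinal models examining all three time points", so time is categorical.

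The only covariate adjustment named for the Aim 1 regressions is "to examine effects after adjusting for potential confounders inadequately balanced". The baseline score of the outcome is not named as a covariate, and no common T0 mean is imposed.

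The primary tests are separate. They use a "97.5% one-sided confidence interval [CI] for cross-sectional T1 responses".

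The sample size section says "For disease specific distress, the baseline standard deviation was 9.31 points", and Table 4 gives "T1 Mean 6.22, SD = 5.72 GC arm T1 Mean 6.00, SD = 6.42 Web arm" for the same outcome. For knowledge, the baseline SD is 2.86 and the T1 SDs are 2.59 (GC) and 2.12 (web).

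**The concern.** In a model with T0, T1 and T2 as responses, time indicators, an arm main effect and arm-by-time terms, the arm coefficient is the T0 difference between arms. The arm-by-T1 coefficient is then the T1 difference minus the T0 difference, which is the difference in mean change. If T0 is unaffected by assignment, its expected value is the same in both arms. Estimating a T0 difference and subtracting all of it therefore adds noise and removes no bias.

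In most trials this cost is moderate. Here the pilot baseline is more variable than T1 on both primary scales, so more noise is imported than usual. The longitudinal part of Aim 1 rests on this model, as do the arm/time/moderator interactions of Aim 3a, where the article itself is concerned to maintain power.

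**Working it through.** **Inputs.** n = 255 per arm (Table 4). Baseline SD s0: knowledge 2.86, distress 9.31. Pooled T1 SD s1 from the two arms in Table 4:
- knowledge √((2.59² + 2.12²)/2) = 2.367
- distress √((5.72² + 6.42²)/2) = 6.080

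The T0-T1 correlation ρ is not in the article. I assume 0.5, with a range of 0.3 to 0.7.

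**Reproducing the plan's own figures.** Table 4 power, with margins 0.45 × 2.86 = 1.287 and 0.20 × 9.31 = 1.862, one-sided 2.5%, power = Φ((margin − effect)/SE − 1.96), SE = s1√(2/255):
- Knowledge, effect −0.7: SE 0.210, power 80.0%; at 0, above 99.9%.
- Distress, effect −0.22: SE 0.538, power 97.2%; at 0, 93.3%.

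These agree with Table 4. With the baseline SDs the values would be 64.0% (knowledge, −0.7), 71.4% and 61.7% (distress). Table 4 therefore rests on raw T1 variability and does not involve the GEE.

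**Variance per person of three T1 contrasts** (each SE = √(2 × variance/255)):
- change from T0 (arm-by-T1 term): s0² + s1² − 2ρ·s0·s1
- raw T1 difference (arm plus arm-by-T1): s1²
- T1 adjusted for T0: s1²(1 − ρ²)

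| Outcome | ρ | Change | Adjusted | Change/adjusted | Change/raw | Raw/adjusted |
|---|---|---|---|---|---|---|
| Knowledge (raw 5.60) | 0.3 | 9.72 | 5.10 | 1.91 | 1.74 | 1.10 |
| | 0.5 | 7.01 | 4.20 | 1.67 | 1.25 | 1.33 |
| | 0.7 | 4.30 | 2.86 | 1.51 | 0.77 | 1.96 |
| Distress (raw 36.97) | 0.3 | 89.68 | 33.64 | 2.67 | 2.43 | 1.10 |
| | 0.5 | 67.04 | 27.73 | 2.42 | 1.81 | 1.33 |
| | 0.7 | 44.40 | 18.85 | 2.36 | 1.20 | 1.96 |

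At ρ = 0.5 the SE falls from 0.235 to 0.182 for knowledge (23% narrower) and from 0.725 to 0.466 for distress (36% narrower).

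**Bound that needs no assumption on ρ.** With k = s0/s1, change/adjusted = 1 + (k − ρ)²/(1 − ρ²). For k > 1 its minimum is at ρ = 1/k and equals k². That is 1.208² = 1.46 for knowledge and 1.531² = 2.34 for distress. The change contrast beats the raw T1 difference only if ρ > k/2, which is about 0.60 (knowledge) and 0.77 (distress).

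**Simulation.** With 3,000 simulated trials of 255 per arm, change/adjusted was 1.91, 1.63 and 1.49 (knowledge) and 2.62, 2.44 and 2.41 (distress) at ρ = 0.3, 0.5 and 0.7. In one data set fitted with the arm-by-time GEE (distress SDs, ρ = 0.5), the arm-by-T1 coefficient equalled the difference in mean change (0.6309) under both independence and exchangeable working correlation. Its SE was 0.704, against 0.457 for T1 adjusted for T0.

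**Does a common T0 mean do the same job?** Such a GEE estimates the T1 difference minus c times the T0 difference, and c depends on the working correlation.
- Independence: c = 0, so the result is exactly the raw T1 difference.
- Unstructured, with its own variance at each time: c = ρ·s1/s0, the adjusted contrast.
- Exchangeable with one common scale: c is the average covariance over the average variance. Taking the T2 SD equal to T1 and all correlations equal to ρ, c = 0.654 for distress at ρ = 0.7, against an optimum of 0.7 × 6.080/9.31 = 0.457. The variance is 18.85 + (0.654 − 0.457)² × 86.68 = 22.2, or 1.18 times the adjusted one. For knowledge at ρ = 0.3 the same sum gives 1.00.

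**The case against.** **The reported contrast is not fixed.** The article says which terms enter the model, not which one is reported. The same fit yields the plain T1 difference. This stands: the 1.5 to 2.7 figures apply only if the interaction terms are read as the effect. The alternative reading still ignores T0, at 1.10 to 1.96 times the adjusted variance.

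**The model is conventional, unbiased and secondary.** This also stands. A reader might infer that the non-inferiority tests or their power are compromised. They are not: both primary tests are cross-sectional at T1, and Table 4 reproduces from the T1 SDs.

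**Constraining the T0 mean is not a remedy by itself.** This is right. Under independence it returns the raw difference, and for knowledge at ρ = 0.7 that is worse than the change contrast (1.96 against 1.51).

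**Equal T0 means are assumed.** The outcomes section does not place T0 relative to randomisation. Table 1 puts a survey request at the end of the pre-disclosure education. The two arm descriptions send people who have not done that education to complete or decline it after the Step 2 Letter, which tells them their arm. If some T0 surveys follow that letter, conditioning on T0 could bias the contrast. Subtracting T0 would distort it too, so this does not defend the present model, but it is a condition on the fix.

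**Aim 3a.** A reader might carry the remedy to every moderator. The article lists intervention usage among them, and use of digital-ROR is post-randomisation. Within usage levels randomisation does not balance T0, so the argument does not reach there.

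**Inputs.** ρ and the T2 SD are not given, and the pilot size is not stated. The bounds of 1.46 and 2.34 do not need ρ, but they do rest on the pilot SDs. No figure can be given for T2.

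**Conclusion.** The point holds as a loss of precision in a secondary analysis. If the arm-by-time terms are taken as the effect, the T1 term has 1.5 to 1.9 times (knowledge) and 2.35 to 2.7 times (distress) the variance of a contrast that uses T0 as a covariate, for ρ between 0.3 and 0.7. The minimum over all ρ is 1.46 and 2.34.

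This rests on the pilot SDs, categorical time, complete or imputed data, and T0 being unaffected by assignment. With dropout and a non-independence working correlation, the equality with the change contrast is approximate.

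The documents do not support a claim of bias, of damage to the primary tests, or of a computed loss at T2.

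**What to change.** - Fit the longitudinal GEE with T1 and T2 as responses, the T0 score as a covariate, and arm, time and arm-by-time terms. Report the arm differences at T1 and at T2.
- If a common-T0-mean model is preferred, name a non-independence working correlation. Unstructured with time-specific variances matches the covariate model at T1; exchangeable comes close; independence gives only the raw difference.
- Confirm that T0 is collected before participants learn their arm, for example by comparing T0 survey dates with Step 2 Letter dates.
- In Aim 3a, use this form for moderators fixed before randomisation, and not for intervention usage.

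The cost is one line of model specification and a date check. No new data are needed, and the primary analysis does not change.

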#### Enrollment goals

Our enrollment goal for the primary non-inferiority aim (Aim 1) is 255 participants per arm. To achieve this goal, up to 2500 PMBB participants (cases and procedural controls) are expected to be contacted.

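### The plain Bonferroni split across the two primary outcomes is valid but needlessly conservative; Holm keeps the same 5% family-wise error rate and gains about 7 to 9 points of power

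*Protocol article*

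**What the plan says.** Under Sample size justification for aim 1, the protocol article sets the level of each primary test: "We chose 2.5% Type I error by applying a Bonferroni correction to a 5% Type I error rate with 2 comparisons". Table 4 then gives power for each outcome separately at that level, with 255 per arm.

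The decision rule is under Primary non-inferiority analyses. It opens with the plural, "For the 2 primary analyses, we will apply non-inferiority tests to examine if access to digital-ROR is non-inferior to GC disclosure". It continues in one sentence, "We will conclude non-inferiority if the upper bound of the randomization effect 97.5% one-sided confidence interval", and that sentence sets a "0.45 standardized difference threshold (i.e., margin) for knowledge and a 0.2 standardized threshold (i.e., margin) for disease-specific distress". Agreement of two analysis sets is also required: "We will only declare non-inferiority if both intention-to-treat and per-protocol analyses are consistent".

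The sample size section describes the aim as a single conclusion: 255 per arm was chosen "so we could conclude non-inferiority of digital-ROR if randomization effects comparing the digital arm to GC arms at T1 do not show" clinically relevant worsening. Under Interim analyses, the article reports that one look has already been taken, after 100 participants per arm had completed the T1 survey, and that it was built to protect the Type I error rate.

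**The concern.** Plain Bonferroni is the simplest way to hold a family-wise rate over two tests, but it is not the most efficient. Once one non-inferiority hypothesis has been rejected, only one remains, and Bonferroni still tests it at half the available level.

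How much is given up depends on how the decision sentence is read, and it can be read in two ways.

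- **Separate claims.** Each outcome can support its own statement. Two tests then need multiplicity control, and Holm provides it at the same 5% with more power.
- **Both required.** Digital return of results is declared non-inferior only if knowledge and distress both pass. Each test can then be run at the full one-sided 5% without raising the overall error above 5%.

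The cost falls mainly on knowledge. At the pilot effect of -0.7 points its power sits almost exactly at 80%, while distress has power to spare. Distress will therefore usually pass first and free the full 5% for knowledge.

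**Working it through.** **Inputs (Table 4 and Enrollment goals)**

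- 255 per arm.
- Knowledge: T1 SDs 2.59 (GC) and 2.12 (web); pilot effect -0.7; margin 0.45 × 2.86 = 1.287 points.
- Distress: T1 SDs 5.72 (GC) and 6.42 (web); pilot effect -0.22, which favours web; margin 0.20 × 9.31 = 1.862 points.
- Correlation between the two test statistics, in the favourable direction: not given. Assumed 0, 0.3 and 0.5.

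**Step 1: reproduce Table 4**

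Power = Φ(room/SE − z), where room is the distance from the assumed effect to the margin and SE = √[(SD₁² + SD₂²)/255].

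- Knowledge SE = √[(2.59² + 2.12²)/255] = 0.2096. Distress SE = √[(5.72² + 6.42²)/255] = 0.5385.
- Knowledge at -0.7: (1.287 − 0.7)/0.2096 = 2.801; Φ(2.801 − 1.960) = 80.0%. Table 4 says above 80%, which the rounded margin of 1.29 gives (80.4%).
- Knowledge at 0: above 99.9%. Table 4: above 99%.
- Distress at -0.22: (1.862 + 0.22)/0.5385 = 3.867; Φ(3.867 − 1.960) = 97.2%. Table 4: above 95%.
- Distress at 0: 1.862/0.5385 = 3.458; Φ(3.458 − 1.960) = 93.3%. Table 4: above 90%.

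Table 4 therefore reproduces at one-sided 2.5% with the T1 SDs.

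**Step 2: what the split buys**

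With two independent tests at 2.5%, the chance of at least one false claim is 1 − 0.975² = 4.94%. At 5% each it is 1 − 0.95² = 9.75%. If separate claims are allowed, some control is needed and Bonferroni supplies it.

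**Step 3: Holm at the same family-wise rate**

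The smaller p-value is compared with 2.5%. If it passes, the larger is compared with 5%. The family-wise rate stays at or below 5%. If both hypotheses of inferiority are true, a false claim needs a first-step rejection, which is the Bonferroni event. If only one is true, it is never tested at more than 5%.

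Written as events:

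- Knowledge passes if p(K) ≤ 2.5%, or if 2.5% < p(K) ≤ 5% and p(D) ≤ 2.5%.
- Both pass if both p-values are ≤ 5% and at least one is ≤ 2.5%.

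At correlation 0 the one-sided 5% powers are Φ(2.801 − 1.645) = 87.6% for knowledge and Φ(3.867 − 1.645) = 98.7% for distress. Hence:

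- Knowledge under Holm: 0.7997 + (0.8761 − 0.7997) × 0.9717 = 0.874.
- Both under Holm: 0.8761 × 0.9868 − (0.8761 − 0.7997) × (0.9868 − 0.9717) = 0.863.

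The other correlations use the bivariate normal distribution.

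| Pilot effects, 255/arm | Correlation 0 | 0.3 | 0.5 |
|---|---|---|---|
| Knowledge, Bonferroni | 80.0% | 80.0% | 80.0% |
| Knowledge, Holm | 87.4% | 87.3% | 87.2% |
| Both, Bonferroni | 77.7% | 78.4% | 78.9% |
| Both, Holm | 86.3% | 86.6% | 86.8% |
| Both, 5% each (valid only if both required) | 86.5% | 86.8% | 87.0% |

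**Step 4: other effects**

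If the true distress effect is 0 and knowledge is at -0.7, power for both is 74.6-77.0% under Bonferroni and 84.3-85.3% under Holm. If both true effects are 0, it is 93.3% and 96.5%, so the gain shrinks to about 3 points.

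**The case against.** The strongest defence is that the plan intends two separate claims. It names two primary analyses, speaks of tests in the plural, counts two comparisons, and gives each outcome its own margin, error rate and power in Table 4. The word joining the two margins may do no more than match each margin to its outcome. On that reading the split is required and works. This defence stands.

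It defeats two stronger readings. A reader might infer that the split loses power for no error control. That is true only if both outcomes must pass, and the text does not settle that. A reader might also infer that Table 4 overstates power because the joint figure is below 80%. The table claims per-outcome power only, and those figures reproduce. Joint power of 78-79% is something it does not report, not an error in it.

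Three practical objections also carry weight.

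- Bonferroni gives simultaneous confidence bounds at one fixed level. Under Holm, the confidence level for the second outcome depends on the first result. This is a real but small cost.
- An interim analysis has been done, so relaxing a level now needs care. This stands as a condition on the change.
- The gain is largest at the adverse knowledge effect of -0.7 and small if the true effects are 0. This is correct, but -0.7 is the effect at which Table 4 shows knowledge power only just above 80%.

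It might also be said that one-sided 2.5% per test is conventional in its own right. The article does not argue that; it derives 2.5% by halving 5%.

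**Conclusion.** The point holds as a matter of efficiency. Testing each outcome at one-sided 2.5% is valid under either reading, and conservative under both. At the plan's own pilot effects, Holm adds about 7 points of knowledge power (80.0% to 87.2-87.4%) and 8 to 9 points of power to meet both margins (77.7-78.9% to 86.3-86.8%). It does so at the same one-sided 5% family-wise rate and with no extra participants.

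These figures rest on normal approximations, the pilot T1 SDs and an assumed correlation of 0 to 0.5. They treat distress as one outcome, as Table 4 does. They leave out the per-protocol requirement, missing data and the interim analysis.

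The two sections do not amount to a proven contradiction, because the decision sentence admits either reading. The article does not say what is concluded if one outcome passes and the other fails. At the pilot effects that has a 19-22% chance under the present split. On its own this is a detail that the full analysis plan may settle, but it should be stated in the same edit because the choice of procedure depends on it.

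**What to change.** 1. Under Sample size justification for aim 1, replace Bonferroni with Holm at a one-sided family-wise rate of 5%. Under Primary non-inferiority analyses, test the outcome with the smaller p-value against its 97.5% one-sided bound and, only if it passes, test the other against its 95% one-sided bound.
2. Say how the p-values are ordered, given that intention-to-treat and per-protocol results must agree. Using the larger of the two p-values for each outcome would fit that requirement.
3. State whether non-inferiority is concluded outcome by outcome or only if both outcomes pass. If both are required, drop the split and test each at one-sided 5%.
4. Add a row to Table 4 with the power to meet both margins and the correlation assumed.
5. Record that the change was made before the final analysis, without use of arm-level results, and that it is consistent with the interim analysis's error control.

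The cost is a few sentences, one table row and a dated amendment, with no new data or participants. The downsides are a confidence level for the second outcome that depends on the first, and the need to show that the interim results did not prompt the change.
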